## Abstract

**Background:**

The global prevalence of diabetes mellitus (DM) continues to rise and 70% of diabetic individuals have dry eye disease (DED) that leads to subsequent abnormalities of the corneal epithelium, corneal nerves, tear film, or corneal endothelium. In addition, persons with diabetes produce fewer tear secretions than healthy individuals. While several anti-inflammatory drug-based therapies for dry eye in diabetic individuals are currently being administered, their efficacy has not been studied in detail. Therefore, the aim of this study was to compare the effectiveness of 3% diquafosol (DQS) vs 0.1% hyaluronic acid (HA) eye drops in diabetic dry eye patients.

**Methods:**

This triple-blind randomized, control trial will include 202 diabetic-related DED and will be assigned to DQS (*n* = 101) and HA (*n* = 101) one drop, six times per day for 8 weeks. Tear film lipid layer, non-invasive breakup time, conjunctivocorneal staining score, corneal sensitivity, tear MMP-9 levels, meibomian gland expression and quality, tear meniscus height, corneal nerves, immune/inflammatory cell change, conjunctival hyperemia, and ocular surface disease index questionnaire score will be assessed and compared at baseline, week 4, and week 8.

**Discussion:**

This study will be a standardized, scientific, clinical trial designed to evaluate the therapeutic effects and safety of DQS and HA for diabetic dry eye treatment.

**Trial registration:**

ClinicalTrials.govNCT05682547. Registered on December 05, 2022.

**Supplementary Information:**

The online version contains supplementary material available at 10.1186/s13063-023-07818-8.

## Administrative information

Please take note that the numerical values enclosed in braces within this protocol pertain to the corresponding item numbers in the SPIRIT checklist. The arrangement of the elements has been altered to cluster comparable items, as per the guidelines outlined in the SPIRIT 2013 Statement that defines standard protocol items for clinical trials. Please refer to (http://www.equator-network.org/reporting-guidelines/spirit-2013-statement-defining-standard-protocol-items-for-clinical-trials/) for further information.

## Introduction

### Background and rationale {6a}

Diabetes mellitus (DM) is a prevalent chronic metabolic illness that causes relative insulin insufficiency in target organs owing to pancreatic β-cell dysfunction and insulin resistance [1]. Shift to a sedentary lifestyle, an aging population and obesity have significantly contributed to the global rise in the prevalence of DM. In 2019, the prevalence of diabetes was documented to be 9.3% (463 million people) and in 2030 it is estimated to rise to 10.2% (578 million) and DM accounts for approximately 90% of all diabetic occurrences [2, 3]. Negative alterations to the tear film, corneal epithelium, corneal endothelium, and corneal nerves have been observed in 47–64% of patients with diabetes [4]. Ocular surface manifestation of signs and symptoms secondary to DM has been termed diabetic keratopathy (DK) [5]. DK has been documented to increase central corneal thickness [6], decrease endothelial cell density, lead to superficial punctate keratitis [7], delay and impede wound repair, and decrease corneal sensitivity due to neuropathy. Furthermore, DM patients have been noted to have compromised tear quantity and quality due to conjunctival goblet cell loss as documented by cytologic analysis. Goblet cells secrete mucin, which stabilizes the tear-film, minimizes tear evaporation, and reduces mechanical friction. Goblet cell loss in animal models suggests that it disrupts the ocular surface’s immune tolerance and increased the expression of inflammatory cytokines in the conjunctiva.

Diquafosol (DQS) is a dinucleotide polyphosphate which is a purinoceptor agonist; when administered to the ocular surface, it binds to P2Y2 receptors and stimulates mucin and tear secretion. The corneal epithelium, conjunctival epithelium, lacrimal gland ductal epithelium, meibomian gland sebaceous cells, and meibomian gland ductal cells all express the P2Y2 receptor. Subsequently, enhanced secretion of mucin and tear secretion due to DQS ophthalmic solution leads to stabilization of the tear film, minimizes tear evaporation, and reduces mechanical friction thereby protecting the corneal epithelium. Various reports have concluded that 3% DQS is effective in the treatment of dry eye disease and the year 2020's findings suggest that DQS improves corneal epithelial damage in DM rat model [8–10].

Around 0.1% hyaluronic acid (HA) used in artificial tears has been reported to promote corneal re-epithelium and improve corneal healing [11]. Additionally, HA has been reported to decrease the rate of tear evaporation and enhance the stability of tear film [12]. HA ophthalmic drops have emerged as a first-line treatment of choice for dry eye disease (DED) [13].

Although the significance of DED related to DM has been acknowledged and however, no clear guidelines for treatment options have been established or recommended [14]. Both DQS and HA eye drops are often prescribed to DED sufferers and are found to be clinically effective. However, these studies did not focus on evaluating the effectiveness of different eye-drop treatments in individuals with DED related to DM.

Therefore, the purpose is to assess and compare the effectiveness of DQS and HA topical eye drops on DM-related DED.

### Objectives {7}

The primary objective of this study is to perform a comparative efficacy assessment between DQS eye drop and HA eye drop in alleviating signs and symptoms of DED in diabetic patients.

### Trial design {8}

This is a prospective, randomized, triple-blind, exploratory, controlled trial design study. Participants will be randomized (1:1) to the DQS group (*n* = 101) or HA group (*n* = 101). Participants in the DQS group will be administered one drop six times per day for 8 weeks (56 days), while the participants in the HA group will receive the assigned treatment over an 8-week period, one drop six times per day as depicted in Fig. 1.

**Fig. 1 Fig1:**
[figure not shown]
Study flowchart

## Methods: participants, interventions, and outcomes

### Study setting {9}

Diabetic patients diagnosed with DED will be recruited at the Department of Ophthalmology, He Eye Specialist Hospital (HESH), Shenyang, China.

### Eligibility criteria {10}

Inclusion criteria are as follows:Age ≥18 years(i) A1c≥6.5% (48 mmol/mol); (ii) fasting plasma glucose ≥126 mg/dL (7.0 mmol/L); and (iii) oral glucose tolerance test and random plasma glucose ≥200 mg/dL (11.1 mmol/L)Able and willing to comply with the treatment/follow-up schedule.Bilateral signs and symptoms of DED: (i) Ocular Surface Disease Index (OSDI) questionnaire ≥13, (ii) non-invasive tear breakup time (NITBUT) ≤ 5 seconds, and (iii) conjunctivocorneal staining score (CS) ≥3 points. The presence of two or more criteria was used to establish a positive DE diagnosis, based on the 2017 Asia Dry Eye Society criteria [15].

Exclusion criteria are as follows:Patients with a history of hypersensitivity to any of the ingredients in DQS and artificial tear drops (ATDs).Participants with systemic immune-mediated illnesses, such as secondary Sjögren’s syndrome or graft-versus-host disease.Patients use topical medication(s) for the treatment of ocular disorders such as glaucoma or allergic conjunctivitis.Previous ocular surgery or trauma.1-month history of blepharal and periorbital skin disease or allergies.Severe dry eye with corneal epithelial defect.Limbic keratitis.Pterygium.Corneal neovascularization.Breastfeeding or pregnant women.Rheumatic immune systemic diseases.Herpes zoster infection.Allergic to fluorescein.Contact lens wearers.Patients with active eye infections.Patients with recurrent corneal erosions.Patients with hereditary corneal disease.Patients with punctal plugs or a history of surgical punctal occlusions.

### Informed consent {26a}

Trained and experienced clinicians will seek informed permission from prospective participants. After taking a detailed dry eye examination, if the potential participant meets the criteria and is willing to proceed to enrolment in the trial, they will sign and date informed consent forms. Here the potential participant will be fully briefed on the objective of the study and the contents of the informed consent form

### Additional consent provisions for collection and use of participant data and biological specimens {26b}

This trial does not involve collecting biological specimens.

### Interventions

#### Explanation for the choice of comparators {6b}

##### Study arm

Participants will use DQS eyedrops, a P2Y2 receptor agonist that promotes tear fluid and mucin secretion.

##### Control arm (active control)

Participants will utilize HA eyedrops as it has been shown to stimulate tear and mucus production on the ocular surface as a first-line treatment of choice for DED.

#### Intervention description {11a}

In this study, patients will receive either DQS (Diquas; Santen Pharmaceutical Co., Ltd., Osaka, Japan) or 0.1% hyaluronic acid (HA) artificial tears (preservative-free) eye drops for 8 weeks based on their randomized group allocation. The dosage for both drugs is 1 drop, 6 times per day. Two follow-up visits were performed on day 28 (4 weeks) and day 56 (8 weeks) in week 8 in both groups, comprehensive eye exams will be conducted by an ophthalmologist including primary outcomes, secondary outcomes, and safety evaluation.

#### Criteria for discontinuing or modifying allocated interventions {11b}

After enrollment in the study, participants will receive one drop of DQS or HA six times per day for 8 weeks (56 days). For very rare cases such as eye secretion, eye irritation, eye itching, congestion, and eye pain, participants will be advised to use the designated eye drops. Adverse events (AE) will be continuously monitored. In the case of an AE, participants will be informed about the severity of the event and the principal investigator (PI) will decide if participants can continue further. If participants consent and agree, they will be reminded daily regarding the administration of eye drops. Any queries regarding the study will be answered by trained clinical staff at HESH, Shenyang, China.

#### Strategies to improve adherence to interventions {11c}

Participants will be reminded by phone or email 1 week prior to their clinical visit; then, appointments will be scheduled in advance according to their availability. In order to improve adherence, patients will be given a medication (eyedrop) record booklet and their medication (eyedrop) status will be checked at each follow-up visit, and investigators will send a text message to remind the participants every day. In the event of non-compliance, such as absence, participants will be contacted by phone or email to confirm their willingness to continue or terminate the study.

#### Compliance

The research will be done on the basis of the intention to treat. On the basis of the eye-drop usage calendar, compliance with eye-drop use will be measured. There is no minimal compliance requirement for eye drop administration that would result in exclusion from the study; nevertheless, compliance will be monitored in statistical analyses and utilized as a gauge of the treatment's acceptability in accordance with the secondary goals. In addition to discussing evidence of overuse with participants, they will be instructed again on correct usage and compliance.

#### Relevant concomitant care permitted or prohibited during the trial {11d}

Any other systemic or topical medication, treatment, or therapy related to dry eye disease will be prohibited during the course of this study.

#### Provisions for post-trial care {30}

There is no anticipated harm and compensation for trial participation but participants who display signs and symptoms of deterioration in their dry eye status will be evaluated by the PI and be directed to their local dry eye center for further evaluation and necessary treatment.

#### Outcomes {12}

Figure 2 displays the timeline for data collection and site visits. The assessments will be conducted in accordance with a predetermined order. After obtaining the subjective symptom score using the  -OSDI) questionnaire [16], a physician will perform an in-person medical examination and lifestyle-related interview. Comprehensive eye exams will be conducted by an ophthalmologist. We plan to use primary and all the secondary outcomes (CS, TFLL score, TMH, RS score, MMP-9 detection, corneal sensitivity score, meibomian gland expression and quality, and corneal nerves and immune/inflammatory cells) to measure improvement which will be compared before (baseline) and after (day 28, day 56) between the groups, except for MMP-9 detection which is only at day 56.

**Fig. 2 Fig2:**
[figure not shown]
SPIRIT figure of enrolment, interventions, and assessments. *t*_*0*_, week 0; *t*_*1*_, week 4; *t*_*2*_, week 8

#### Primary outcomes

NITBUT: The Keratograph 5M (Oculus, Germany) topographer will assess non-invasive tear breakup time. Three sequential readings will be captured, and the median value will be included in the final analysis. The median value will be recorded [17].

#### Secondary outcomes

CS: Fluorescein and lissamine staining of the ocular surface will be divided into three zones comprising nasal conjunctival, corneal, and temporal conjunctival areas. The staining score ranged from 0 to 3 for each zone, yielding a total score of 0–9 for the ocular surface [15].

Tear film lipid layer (TFLL) score: Tear film lipid layer interferometry will be assessed using DR-1 (Kowa, Nagoya, Japan). The results will be graded as follows: grade 1, somewhat gray color, uniform distribution; grade 2, somewhat gray color, nonuniform distribution; grade 3, a few colors, nonuniform distribution; grade 4, many colors, nonuniform distribution; grade 5, corneal surface partially exposed [18, 19].

Corneal Sensitivity Score: Corneal sensitivity score measured with a Cochet-Bonnet esthesiometer (in mm filament length); the measurements will be done 3 times at every assessment session and the median value will be recorded [20].

Matrix metalloproteinase 9 (MMP-9) detection: Inflammation Dry (Rapid Pathogen Screening Inc., Sarasota, FL, USA) is a patented and proprietary modification of a traditional lateral flow device and uses direct sampling microfiltration technology. Two antigen-specific antibodies capture MMP-9 antigens in the sample, and this complex is captured in a proprietary mode at the test result line, giving rise to a visually observable signal [21, 22].

Tear meniscus height (TMH): Tear meniscus height using the Keratograph 5M (Oculus, Germany) topographer will be measured three times consecutively and the median value was recorded [17].

Conjunctival hyperemia (RS score): Conjunctival hyperemia (RS score) will be assessed by Keratograph image (Oculus, Germany) of 1156 × 873 pixels, with redness score (RS) ranges from 0.0 (normal) to 4.0 (severe) [23].

Meibomian quality and meibomian gland expressibility: Meibomian quality will be assessed under a slit-lamp; eight meibomian glands in the middle parts of the eyelid will be assessed using a scale of 0 to 3 for each gland (0 represented clear meibum; 1 represented cloudy meibum; 2 represented cloudy and granular meibum; and 3 represented thick, toothpaste-like consistency meibum). Meibomian gland expression: five meibomian glands in the middle part were evaluated on a scale of 0–3: 0, all glands expressible; 1, 3–4 glands expressible; 2, 1–2 glands expressible; and 3, no glands expressible.

Corneal nerves and immune/inflammatory cell change: HRT III RCM (Heidelberg Engineering GmbH, Germany) will be used to record corneal nerves and immune/inflammatory cell change [24]. A total of 5–8 sequence/volume scans were taken from the center of each cornea, focusing on all corneal layers: superficial, intermediate, and basal epithelial layers; sub-basal nerve plexus, anterior, central, and posterior stroma; and endothelium. Three representative images of the subbasal nerve plexus and epithelial DCs will be selected for analysis for each eye, considering criteria such as a whole image in the same layer, best focus, and good contrast.

OSDI: the Chinese language-validated OSDI, which is a questionnaire consisting of 12 questions for evaluating the effects of dry eye syndrome on vision, ocular symptoms, and any condition associated with DED, will be used [16]. The patient will answer each question on a scale ranging from 0 to 4, with 0 indicating “none of the time” and 4 indicating “all of the time.” If a certain question is deemed irrelevant, it will be marked as “not applicable (N/A)” and excluded from the analysis. The OSDI total score is calculated according to the proprietary formula proposed by the authors of the original OSDI [25]. The scale ranges from 0 to 100, with higher scores representing more severe cases of DED.

### Participant timeline {13}

The schedule for data collection and visits is shown in Fig. 2. After registration for this study, the assigned treatment intervention will be administered for 8 weeks. Furthermore, the effect of eyedrops will be examined during the 4-week and 8-week follow-up period (Fig. 1).

### Sample size {14}

The sample size calculation is based on the primary outcome measures, named NITBUT, to establish the non-inferiority between the groups in terms of the changes in the mean from the baseline at day 56. For the NITBUT, a sample size of 164 subjects, 82 in each group, is sufficient to detect a clinically important difference of 5.24 s [26] between groups in reducing DED assuming a standard deviation of 5.23 s [27] using a two-tailed *t*-test of difference between means with a power of 80% and a level of significance of 5%. Considering a dropout rate of 10% the sample size required is 182 (91 per group). With an additional 10% compensation for the potential deviation of dry eye metrics from a normal distribution [26, 27], the sample size required is 202 (101 per group).

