### Statistical methods

#### Statistical methods for primary and secondary outcomes {20a}

In this research, unless otherwise mentioned, the significance level is set to 5% two-sided and the confidence coefficient is set to 95%. The demographic data of the study’s subjects will be tabulated by calculating the mean and standard deviation for continuous variables and the frequency and percentage for categorical variables. If the continuous variables do not follow a normal distribution, they will be converted appropriately by logarithmic transformation or other means and aggregated with the mean and standard deviation, or the median and interquartile range will be utilized as descriptive statistics.

The safety analysis will be conducted based on a safety analysis population that includes subjects who have received at least one dose of medication after randomization.

Data will be collected for all patients participating in the treatment at the following stages: baseline, first follow-up at week 4 (day 28), and second follow-up at week 8 (day 56 ). The primary outcome measures for this study are NITBUT scores before and after treatment. For the main endpoint, between-group comparisons using baseline as a covariate and an analysis of covariance will be done to produce the adjusted mean, its 95% confidence interval, and the *p*-value. A paired *t*-test will be used to make within-group comparisons. To ensure participant safety, frequencies and proportions will be computed for each group and item, and comparisons between groups will be made using Fisher’s exact probability test or the *χ*^2^ statistic.

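### The sample-size section claims non-inferiority, but it sizes a two-tailed test of difference and no margin, direction or decision rule is given

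*Protocol article*

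**What the plan says.** The protocol article's Sample size {14} section gives the purpose of the calculation, for the primary outcome NITBUT, as "to establish the non-inferiority between the groups in terms of the changes in the mean from the baseline at day 56". The following sentence says that 82 subjects per group (164 in total) "is sufficient to detect a clinically important difference of 5.24 s", "assuming a standard deviation of 5.23 s", "using a two-tailed *t*-test of difference between means" and "with a power of 80% and a level of significance of 5"%. Two 10% inflations then bring the total to 182 and 202.

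The term non-inferiority appears nowhere else. Objectives {7} sets out to "perform a comparative efficacy assessment between DQS eye drop and HA eye drop". Trial design {8} reads "This is a prospective, randomized, triple-blind, exploratory, controlled trial design study". Statistical methods {20a} sets a two-sided 5% level and says of the main endpoint that "between-group comparisons using baseline as a covariate and an analysis of covariance will be done to produce the adjusted mean", together with its 95% confidence interval and a p-value. It names no margin.

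**The concern.** Two adjacent sentences state incompatible hypotheses. A non-inferiority design asks whether one named treatment is worse than the other by less than a pre-specified margin, and it answers with a confidence limit. A two-tailed test of difference asks whether the means differ in either direction. The sample-size section names the first and calculates for the second. It does not say which drug is to be shown not inferior.

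What is at stake is the trial's main conclusion. HA is an active control that the article calls a first-line treatment, so a small observed difference is quite possible. If the primary p-value then exceeds 0.05, the stated aim invites a report of non-inferiority. A non-significant test of difference does not show that, because it is also what an imprecise comparison produces. A margin chosen once the data are known would not repair the claim.

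**Working it through.** **Inputs.** Difference 5.24 s, SD 5.23 s, two-sided 5%, power 80% and 82 evaluable per group, all from Sample size {14}; 1:1 allocation from Trial design {8}. The article does not say whether 5.23 s is the SD of a single reading or of the change, so I take it as the SD of the day-56 change. z(0.975) = 1.960 and z(0.80) = 0.842.

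**1. The plan's own figure.** n per group = 2 × (1.960 + 0.842)² × SD² / difference²
= 2 × 7.85 × (5.23/5.24)² = 15.6, so 16 per group. The exact t-test gives 17 (power 80.9%). The stated 82 is not reproduced. Variants tried, per group:

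| Variant | n |
|---|---|
| One-sided 5% | 13 |
| 90% power | 21 |
| 95% power | 26 |
| SD × √2 | 32 |
| SD × 2 | 63 |
| Rank-test efficiency 0.864 | about 19 |
| 5.24 s read as a non-inferiority margin | 16 |

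None reaches 82. An SD of about 12.0 s would be needed to require 82 for 5.24 s. The inflation steps do follow to within rounding: 164/0.9 = 182.2 and 182/0.9 = 202.2.

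**2. Precision with 82 per group.** SE = 5.23 × √(2/82) = 0.817 s. The 95% half-width is 1.96 × 0.817 = 1.60 s.

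**3. The margin that 82 per group could serve.** With true difference 0 and one-sided 2.5%, the smallest margin at 80% power is (1.960 + 0.842) × 0.817 = 2.29 s. The protocol gives no margin, so those below are assumptions that show the range:

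| Assumed margin (s) | Evaluable n per group for 80% power | Power with 82 per group |
|---|---|---|
| 1.0 | 430 | 23% |
| 1.5 | 191 | 45% |
| 2.0 | 108 | 69% |
| 2.5 | 69 | 87% |
| 3.0 | 48 | 96% |

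If all 101 randomised per group were evaluable, the smallest margin would be 2.06 s.

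**4. The sections side by side.**

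| Section | Framework | Margin or rule |
|---|---|---|
| Sample size {14}, first sentence | Non-inferiority | None |
| Sample size {14}, second sentence | Two-tailed difference | Not applicable |
| Objectives {7} | Comparative efficacy | None |
| Trial design {8} | Exploratory, controlled | None |
| Statistical methods {20a} | Two-sided 5% ANCOVA with 95% CI and p-value | None |

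Only one sentence speaks of non-inferiority. Everything else is consistent with an ordinary two-sided comparison.

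**The case against.** The best defence is that this is one stray phrase. The objective, the design statement, the test used for sizing and the primary analysis all describe a two-sided comparison, and nothing says that a non-significant p-value will be read as non-inferiority. That is probably the right account of how the phrase arose, and it is why the repair is cheap. It does not remove the defect, because the phrase is the article's only explicit statement of the primary hypothesis. Nor can the gap be left to an analysis plan: a margin is an input to a non-inferiority sample size, and the conflict lies within one section.

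A second objection is that the analysis is more than a p-value. This stands. A two-sided 95% confidence interval for the adjusted difference is the usual basis for a one-sided 2.5% non-inferiority decision, so the missing margin is the decisive gap and ANCOVA is not at fault. The lack of a per-protocol analysis is not held against the article either, since that is commonly left to an analysis plan.

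A reader might infer more than the article supports:

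- **That 5.24 s is the margin.** With that margin, SE 0.817 s and a true 3 s deficit for DQS, non-inferiority would be declared with probability Φ((5.24 − 1.60 − 3.0)/0.817) = 0.78. But the article calls 5.24 s a difference to detect and states no 3 s deficit. The result also depends on an SD and n that do not fit together: with an SD near 12.0 s, SE is about 1.87 s and the probability falls to about 0.22.
- **That 5.24 s exceeds an entry limit of 5 s.** NITBUT of 5 s or less is one of three criteria in Eligibility {10}, of which two suffice, so patients can enter above it.
- **That 2.29 s is a ceiling for the margin.** It is the smallest margin that 82 per group serves at 80% power. A smaller one needs more patients, and a margin should not be derived from a sample size already chosen.

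**Conclusion.** The point holds: the hypothesis in the sample-size section is wrong as written. It contradicts the test used to size the trial, and no margin, direction or rule exists by which non-inferiority could be judged. The plan as it stands cannot support that conclusion, although the gap can be closed before unblinding.

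In size, the planned evaluable number gives a 95% half-width of about 1.60 s and at least 80% power only for margins of about 2.29 s or more. These figures assume that the SD of 5.23 s applies to the day-56 change, a true difference of 0, one-sided 2.5%, the normal approximation and no gain from baseline adjustment. They carry a caution, because the stated difference and SD call for about one fifth of the stated sample (16 to 17 against 82 per group), so at least one input or the method is misreported. The contradiction itself depends on none of this arithmetic.

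**What to change.** **Preferred.** In Sample size {14}, delete the non-inferiority wording. State there and in Statistical methods {20a} one hypothesis: a two-sided 5% test of the DQS minus HA difference in NITBUT change from baseline to day 56, by ANCOVA with baseline as covariate, reported with its 95% confidence interval. Add that a non-significant result will not be reported as non-inferiority or equivalence. This costs wording only and needs no new data.

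**If non-inferiority is really intended.** Before unblinding, state which drug is to be shown not inferior, give a margin with its clinical justification, and base the decision on the relevant limit of the 95% confidence interval for the adjusted difference. Recompute the sample size from that margin. This is more than wording: on the stated SD, a 2.0 s margin, for example, needs 108 evaluable per group before inflation.

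**In either case.** Check 5.24 s, 5.23 s and the calculation method against their sources, say whether the SD is that of the change, and correct whichever is misreported, so that the stated sample size can be reproduced. The protocol's own amendment section {25} requires a revised protocol to go to the ethics committee when analyses are modified.

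### The sample-size inputs for NITBUT (difference 5.24 s, SD 5.23 s, two-tailed 5%, 80% power) require 17 per group, not the stated 82, so difference, SD, power and size cannot all be right

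*Protocol article*

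**What the plan says.** The section Sample size {14} of the protocol article gives a complete calculation for the primary outcome, NITBUT:

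- Size and difference: "a sample size of 164 subjects, 82 in each group, is sufficient to detect a clinically important difference of 5.24" s.
- Spread: "assuming a standard deviation of 5.23 s".
- Test: "using a two-tailed" t-test comparing two means, "with a power of 80% and a level of significance of 5" per cent.
- Aim: "to establish the non-inferiority between the groups in terms of the changes in the mean from the baseline at day 56".
- Inflation: 10% for dropout takes 164 to 182 (91 per group). A further 10% for non-normality takes 182 to 202 (101 per group).

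Allocation is 1:1 (Trial design {8}). The difference and the SD are each referenced to an outside source. No non-inferiority margin is given apart from the 5.24 s.

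**The concern.** Difference and SD are almost equal, so the design effect is one full standard deviation. An effect of that size needs fewer than 20 per group at 80% power, yet the plan asks for 82. Every input needed for the check is printed in one sentence, so the mismatch lies inside the document and does not depend on an unseen analysis plan.

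The traceability of the design is at stake. If both 5.24 s and 5.23 s are right, the stated justification supports roughly a fifth of the planned enrolment. If one of them is misprinted, the difference that the trial was really built to detect is unknown. The two cases lead to very different trials. With an SD of 5.23 s, 82 per group has 80% power for 2.30 s. With an SD near 11.9 s, it has only about 23% power for the same 2.30 s. A reader cannot tell which trial is being run.

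**Working it through.** **Inputs**, all from Sample size {14} except allocation (Trial design {8}): Δ = 5.24 s, SD = 5.23 s, two-sided α = 0.05, power = 0.80, ratio 1:1, stated n = 82 per group.

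**1. Attempt to reproduce 82**

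Standardised difference: d = 5.24/5.23 = 1.002.

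Normal approximation: n = 2(z₀.₉₇₅ + z₀.₈₀)² / d² = 2 × (1.960 + 0.842)² × (5.23/5.24)² = 15.6, so 16 per group.

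Exact two-sample t-test (noncentral t): n = 16.66, so **17 per group, 34 in total**. Power is 80.9% with 17 and 78.3% with 16.

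The stated 82 is not reproduced; 82/17 = 4.8.

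**2. What 82 per group delivers**

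- Power for 5.24 s at SD 5.23 s: 99.9995%.
- Difference detectable with 80% power at SD 5.23 s: standardised 0.440, and 0.440 × 5.23 = **2.30 s**. The normal approximation gives 2.802 × 5.23 × √(2/82) = 2.29 s. With 101 per group it is 2.07 s.
- SD at which 82 per group gives 80% power for 5.24 s: 5.24/0.440 = **11.9 s**.
- Power for 2.30 s if the SD were 11.9 s: d = 2.30/11.9 = 0.193, power about 23%.

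**3. Could another reading give 82?** Exact t, rounded up, per group:

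| Reading | n per group |
|---|---|
| One-sided 5%, 80% power | 14 |
| Two-sided 5%, 90% / 95% / 99% power | 22 / 27 / 38 |
| Two-sided α = 0.005, 80% power | 29 |
| 5.24 s as non-inferiority margin, true difference 0, one-sided 2.5%, 80% power | 17 |
| SD × √2 (change score built from two uncorrelated visits), 80% / 90% power | 33 / 43 |
| SD × 2, 80% / 90% power | 64 / 85 |

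Only doubling the SD and also raising power to 90% comes near 82, and that contradicts two stated inputs. The allowance for non-normality cannot be hidden in the 82 either, because the section applies it later as a separate step.

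**4. The inflation steps**

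82/0.9 = 91.1 and 91/0.9 = 101.1, so 91 and 101 follow from 82 apart from rounding. The mismatch therefore sits in the base figure or its inputs, and the later totals carry it forward. The same two steps from 17 give 17/0.9 = 18.9 (19), then 19/0.9 = 21.1 (21 or 22) per group. That is 42 to 44 in total, against 202.

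**The case against.** The best defence is that the sentence is literally true: 82 per group is sufficient for 5.24 s, and far more than sufficient. The discrepancy runs towards more power, the primary endpoint and its analysis of covariance are untouched, and only wording has to change. All of that stands. It does not rescue the statement, because the sentence ties 82 to 80% power and the section then presents 182 and 202 as sizes that are required.

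A reader might infer more than the documents support, in four ways:

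- **That 5.24 s is impossible because entry requires NITBUT of 5 s or less.** Eligibility criteria {10} asks for two or more of three dry-eye criteria, so a participant can qualify on OSDI and staining with a longer NITBUT. A ceiling on the baseline value would not cap the change from baseline in any case. Whether 5.24 s is a realistic gap between two active drops is a clinical question that rests on a source not shown here.
- **That a non-significant result could not be read against 5.24 s.** With SD 5.23 s and 82 per group, the standard error is 5.23 × √(2/82) = 0.817 s and the 95% half-width is 1.975 × 0.817 = 1.61 s. A non-significant estimate lies within 1.61 s of zero, so its interval reaches at most about 3.2 s and excludes 5.24 s. On the stated inputs such a result would be informative.
- **That 5.24 s is the wrong figure.** The document does not show whether the difference, the SD or the size was misreported. The 2.30 s is solved backwards from 82 and has no source in the protocol.
- **That the trial is underpowered, or that enrolment should be cut.** Neither follows until the inputs are known.

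**Conclusion.** The point holds as an internal arithmetic contradiction. On the printed inputs the requirement is 17 per group (34 in total) against 82 (164) stated, a factor of 4.8. Power at the stated size is over 99.99%, not 80%. At least one of difference, SD, power and size is misreported, and 182 and 202 rest on the same line.

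The conclusion assumes only the test that the section names: an unpaired comparison of two means with equal groups and a common SD. It does not depend on which source figure is right, and none of the alternative readings tried gives 82. Baseline adjustment in the planned analysis of covariance would normally lower the residual variance, so it cannot explain a larger number.

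This should be corrected, because the size and power of the primary comparison are wrong as written and can be put right cheaply. The non-inferiority wording beside a two-tailed test of difference is a further inconsistency in the same section. Reading 5.24 s as the margin does not resolve the arithmetic.

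**What to change.** Leave enrolment at 202. Retrieve the original calculation and rewrite the paragraph in Sample size {14} with the inputs actually used, so that difference, SD, power and n agree and each source figure is attached to the right quantity.

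- **If SD 5.23 s is confirmed:** state that 82 evaluable participants per group have 80% power, at two-sided 5%, for a between-group difference of 2.30 s in the change in NITBUT at day 56, and over 99.99% power for 5.24 s. Describe 2.30 s as a detectable difference. If it is to serve as the design target, give a clinical reason for it separately.
- **If another SD or difference was used:** print that value and its source. At 5.24 s and 80% power, 82 per group corresponds to an SD of about 11.9 s.

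While the paragraph is open, make its stated aim (non-inferiority or difference) match the calculation it reports. The cost is one paragraph and a search of the design file; enrolment, endpoint and schedule do not change.
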